**Figure 2 F2:**
[figure not shown]
MAMMA© study design.

**Table 2 T2:** Adherence to intervention by intervention and control groups

	**Intervention group n(%)**	**Control group n(%)**
No. of reviews recommended by intervention pharmacist		
No. of asthma action plans up taken		
No. of recommended medication changes up taken		

### Control (UCG participants)

The control group will receive usual medical care; this normally includes their regular antenatal visits ranging from weekly to monthly depending on trimester and other complications. They will not receive the intervention, any additional monitoring or education sessions like participants in the MCG. If during follow ups at three and six months, their asthma control becomes a concern (2 or more documented exacerbations without resolution (i.e. increasing preventer dose) since prior assessment or their ACQ score exceeds 2, the participant and their family physician will be notified (with participant permission). This notification will be taken into account when we do the analysis.

Both groups will be given a summarised version of the “Asthma and Healthy Pregnancy” brochure from the Asthma Foundation of New South Wales, Australia which is a pamphlet on basic asthma facts to avoid unfair disadvantage to participants in the control group and to minimise the risks of poorly controlled asthma.

### Follow up

ACQ scores, asthma-related hospital visits and days off work, oral corticosteroid use and preventer to reliever use ratios will be compared at three and six months between groups. Both groups will be assessed using the same data collection form at 3 and 6 months (once in their second trimester and once in their third trimester) and the results will be compared. The assessor collecting the data at three and six months in both groups will be different from the intervention pharmacist and will be blinded to participant group allocation. The assessor will not be given any clinical information about each participant and will be unaware of the study protocol (including details of the intervention) just in case a participant inadvertently discloses details to the assessor. Pregnancy and neonatal outcomes will be confirmed via medical records shortly after delivery.

### Sample size calculation

This is a pilot study, however sample size was still calculated to guide recruitment. Using a conservative standard deviation of 0.66, to detect a change in ACQ score of 0.5 or more between groups,
[18] a sample size of 29 per arm would have 80% power with a two sided 5% significance level assuming the two variances are the same. To allow for 20% attrition, 35 participants will be recruited in each arm.

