### Inclusion and exclusion criteria

All pregnant women with asthma attending antenatal outpatient clinics who are in their first or second trimester, and who can communicate in English will be considered. Patients who are under the age of 18 years or who have not had asthma symptoms (wheeze, chest tightness and/or use of their reliever asthma medication) in the last year will be excluded. Participants who are also unlikely to meet the demands of the trial will be excluded (e.g. planning to relocate during the trial). Furthermore, participants who were previously involved in our previous qualitative exploratory study conducted at the same maternity hospital, titled “Asthma during pregnancy; the experiences, concerns and views of pregnant women with asthma”
[22] will also be excluded. Lastly, in the event of a miscarriage or termination of pregnancy, the participant will be excluded from the trial. Participant characteristics will be described in Table 
1.

**Table 1 T1:** Demographic and clinical characteristics of the study population at baseline

**Characteristic**	**Intervention group (n=30)**	**Control group (n=30)**
Patient information		
Age in years Mean [SD]		
Parity		
Gravidity		
Gestational age at first visit in weeks Mean [SD]		
Height in cm Mean [SD]		
Adherence Score Median [IQR]		
Ethnicity		
Australian		
Arabic		
Asian		
European		
Other		
Asthma severity^+^		
Intermittent to Mild		
Moderate to Severe		
Asthma medication		
SABA only		
ICS+SABA		
ICS/LABA + SABA		
FEV_1_ in litres Mean [SD]		
FEV_1_%predicted Mean [SD]		
FEV_1_/FEV_6_ Mean [SD]		
Co-morbidity		
Gestational diabetes		
Hypertension in pregnancy		
Anxiety/depression		
Other		
Smokers		
Health Care Concession Card holders		

ICS – inhaled corticosteroid, LABA- Long acting beta agonist, SABA – short acting beta agonist.

^+^Asthma severity classified by National Asthma Handbook
[28].

Values are given as number (percentages) unless specified.

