### Data analysis

The primary analysis will be intention to treat. Per protocol analyses will also be conducted. The baseline characteristics of participants in the intervention and control groups will be compared using Chi-square, Student *t*-test or Mann–Whitney tests if distributional assumptions are not satisfied. ACQ scores at baseline, three and six months will be compared using Mann–Whitney test. Secondary outcomes will be listed as descriptive statistics and analysed using similar tests. FEV_1_/FEV_6_ trends will be described as these are observational data only. Sensitivity and predictive validity of the ACQ would also be investigated.

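### The 20% attrition allowance is miscalculated: 35 recruited per arm leaves 28, one short of the protocol's own 29 (minor)

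*Protocol article*

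**What the plan says.** The Sample size calculation section of the protocol article gives these inputs and results:

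- Spread: "Using a conservative standard deviation of 0.66".
- Target difference: "to detect a change in ACQ score of 0.5 or more between groups".
- Result before attrition: "a sample size of 29 per arm would have 80% power with a two sided 5% significance level", with equal variances assumed in the two arms. The test behind this figure is not named.
- Recruitment: "To allow for 20% attrition, 35 participants will be recruited in each arm".

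The same section presents the calculation as guidance for recruiting to a pilot. The Discussion nevertheless says that the trial is powered for its asthma symptom endpoint.

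The Data analysis section says of the primary outcome: "ACQ scores at baseline, three and six months will be compared using Mann–Whitney test". No condition is attached to that choice. The t-test is named only for baseline characteristics.

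The empty shells of Tables 1 and 3 carry n=30 per arm in their column headings. Table 3 repeats it at baseline, three months and six months.

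**The concern.** An attrition allowance has one job: after the stated loss, the number left should still meet the stated requirement. Here it does not, by the protocol's own figures. Anyone who budgets for 20% loss on the strength of this section will believe that 29 per arm are protected when 28 are.

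A second, softer question is which test the stated power belongs to. The figure looks like a t-test figure, while the planned comparison of ACQ scores is a rank test. At stake is the accuracy of a printed power statement, not the validity of the trial.

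**Working it through.** **Inputs** (Sample size calculation section): difference 0.5, common SD 0.66, two-sided 5%, 80% power, 29 per arm required, 20% attrition, 35 per arm recruited. Allocation is 1:1 (Study design section).

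**1. Reproduce the 29.**
Standardised difference: 0.5 / 0.66 = 0.758.
Normal approximation: n = 2 × [0.66 × (1.960 + 0.842) / 0.5]² = 27.35, so 28.
Equal-variance t-test, power from the noncentral t distribution with 2n − 2 degrees of freedom and noncentrality 0.758 × √(n/2):

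| n per arm | t-test power |
|---|---|
| 28 | 79.5% |
| 29 | 80.9% |

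The smallest n that reaches 80% is 29, so the stated figure reproduces exactly as a t-test size. Together with the equal-variance wording, this is the basis for inferring a t-test. It remains an inference.

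**2. Reproduce the 35.**
29 × 1.2 = 34.8, so 35. This matches the stated recruitment.

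**3. Check what the 35 delivers.**
- Left after 20% loss: 35 × (1 − 0.20) = 28, against 29 required.
- Number needed to keep 29 after 20% loss: 29 / 0.8 = 36.25, so 37 per arm (74 in total, against 70).
- Attrition that 35 can absorb while keeping 29: 1 − 29/35 = 17.1%.
- t-test power lost between 29 and 28 per arm: 80.9% − 79.5% = 1.4 points. The result is 0.5 points below the stated 80%.

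**4. Power of the planned Mann–Whitney test.**
The article gives no distribution for ACQ scores, so one has to be assumed. Two routes were used for normal scores with SD 0.66: simulation with 40,000 replicates per n (continuity-corrected), and scaling n by the large-sample efficiency 3/π = 0.955.

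| n per arm | Simulation | Efficiency 0.955 |
|---|---|---|
| 28 | 77.2% | 77.6% |
| 29 | 78.4% | 79.1% |
| 30 | 80.0% | 80.4% |

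Under normality the rank test therefore sits 2 to 3 points below 80% at 28 per arm and 1 to 2 points below at 29.

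The direction depends on the assumption. At the lowest possible efficiency for a shift in location (0.864), power at 28 is about 73%. With an illustrative right-skewed distribution (gamma, shape 2, SD 0.66, shifted by 0.5), simulation at 28 per arm gives about 89% for Mann–Whitney and about 80% for the t-test.

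**The case against.** **The 35 could be right.** A normal-approximation size of 28 gives 28 / 0.8 = 35 exactly, so the recruitment figure might have been correctly inflated from 28. This does not rescue the text, because the section prints 29 as its requirement and 35 does not protect 29 at 20% loss.

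**The effect is trivial and this is a pilot.** The shortfall is one evaluable woman per arm and half a point below 80% by t-test. That stands, and it is why the point is minor. It does not remove the point: the article describes the trial as powered for its asthma endpoint, so the figures behind that description should agree with each other.

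**The rank test may lose nothing.** Sizing by t-test and analysing by rank test is common practice, and with skewed scores Mann–Whitney can be the more powerful of the two. That also stands. A reader might infer that the planned test leaves the trial short of 80% power. The documents do not support this as a plain statement, because the shortfall holds under normal scores and the article says nothing about the shape of the ACQ distribution.

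**The n=30 headings are placeholders.** They sit in empty tables to be filled with actual counts. A reader might infer a rival recruitment target of 30, which would leave 24 after 20% loss, or might infer that no losses are expected between visits. Neither follows: the Sample size calculation section plainly states 35 recruited per arm, and nowhere is 30 given as a target. Nor do 29 and 35 contradict each other by being different, since one counts evaluable women and the other recruited women.

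**Conclusion.** The attrition statement is wrong as written, and the error is minor. Recruiting 35 per arm covers attrition of up to 17.1%, not 20%; at 20% the trial has 28 evaluable per arm and 79.5% power by equal-variance t-test. This part rests only on the protocol's own numbers.

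The remark about the test is weaker and rests on two assumptions: that the 29 came from a t-test, which the reproduced figure and the equal-variance wording suggest, and that ACQ scores are normal with SD 0.66. Under both, the planned Mann–Whitney comparison has about 77% power at 28 and 78% at 29. It deserves a clarifying sentence and does not show that the trial is underpowered. The n=30 headings call for a tidy-up only.

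**What to change.** Replace the attrition sentence in the Sample size calculation section with wording such as: *Recruiting 35 per arm gives 29 evaluable per arm if attrition is at most 17%; at 20% attrition, 28 evaluable per arm give 79.5% power by two-sample t-test.*

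Add a sentence that names the test behind the 29. If it was the equal-variance t-test, add that the Mann–Whitney test planned for ACQ has about 77% power at 28 and 78% at 29 per arm if scores are normal with SD 0.66, and possibly more if they are skewed.

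In Tables 1 and 3, replace n=30 with the number randomised and the number observed at each visit.

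The cost is a few sentences and some column headings. The stated power becomes slightly less favourable. No extra recruitment and no change to the analysis are needed.

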### Data analysis

The primary analysis will be intention to treat. Per protocol analyses will also be conducted. The baseline characteristics of participants in the intervention and control groups will be compared using Chi-square, Student *t*-test or Mann–Whitney tests if distributional assumptions are not satisfied. ACQ scores at baseline, three and six months will be compared using Mann–Whitney test. Secondary outcomes will be listed as descriptive statistics and analysed using similar tests. FEV_1_/FEV_6_ trends will be described as these are observational data only. Sensitivity and predictive validity of the ACQ would also be investigated.

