**Methods/design:**

A pilot single-blinded parallel-group randomized controlled trial testing a Multidisciplinary Approach to Management of Maternal Asthma (MAMMA©) which involves education and regular monitoring. Pregnant women with asthma will be recruited from antenatal clinics in Victoria, Australia. Recruited participants, stratified by disease severity, will be allocated to the intervention or the usual care group in a 1:1 ratio. Both groups will be followed prospectively throughout pregnancy and outcomes will be compared between groups at three and six months after recruitment to evaluate the effectiveness of this intervention. Outcome measures include Asthma Control Questionnaire (ACQ) scores, oral corticosteroid use, asthma exacerbations and asthma related hospital admissions, and days off work, preventer to reliever ratio, along with pregnancy and neonatal adverse events at delivery. The use of FEV_1_/FEV_6_ will be also investigated during this trial as a marker for asthma control.

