**Discussion:**

If successful, this model of care could be widely implemented in clinical practice and justify more funding for support services and resources for these women. This intervention will also promote awareness of the risks of poorly controlled asthma and the need for a collaborative, multidisciplinary approach to asthma management during pregnancy. This is also the first study to investigate the use of FEV_1_/FEV_6_ as a marker for asthma control during pregnancy.

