### Intervention (MCG participants)

The Multidisciplinary Approach to Management of Maternal Asthma (MAMMA©) intervention will embrace a collaborative approach involving the participant’s family physician, pharmacist and asthma educator. Details of the intervention are described in Figure 
2. Asthma education, monitoring, feedback and follow-up are integral components of the monthly intervention. Every month, participants in the intervention group will be contacted by the trial’s nominated pharmacist for an hourly session to assess their asthma control by administrating the Asthma Control Questionnaire (ACQ)
[29] and a short data collection form which inquires about oral corticosteroid use, asthma related hospital admissions, days off work and preventer to reliever use ratio. The ACQ states that an increase in a score of 0.5 is a clinically significant deterioration of asthma control
[29]. The trial pharmacist will provide feed back to the participant’s nominated family physician if the ACQ score has increased by 0.5 or greater and if there has been a documented exacerbation since the last monthly visit. The pharmacist and family physician will then collaborate on appropriate step up therapy for the participant. It is anticipated that this close monthly monitoring will maintain the participant’s asthma under closer control during pregnancy. Each participant in the MCG will be given a handheld device (PiKo-6) to use as they please for home monitoring of lung function and instruction in the use of PiKo-6. They will also receive pharmacist led medication management review at the beginning of the trial, periodic review of inhaler device technique by asthma educator, trigger avoidance and smoking cessation support (if relevant). The MCG will also have their FEV_1_/FEV_6_ measured monthly during the trial. Adherence and uptake of the intervention will be described in Table 
2.

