[30], a target range for FEV_1_/FEV_6_ measurements during pregnancy could be identified and prompt further research in using this ratio as a marker for asthma control during pregnancy. FEV_1_/FEV_6_ could be a simple and easier method of assessing asthma control and help prescribers better distinguish between asthma symptoms and the shortness of breath associated with pregnancy. Women will have the convenient option of monitoring their asthma at home using a handheld spirometer and adjusting therapy or management according to an individualised asthma action plan.

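### FEV1/FEV6 is to be investigated as a marker of asthma control, but the stated analysis only describes its trends and never relates it to control (minor)

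*Protocol article*

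**What the plan says.** **The aim.** The Methods/design part of the abstract states: "The use of FEV_1_/FEV_6_ will be also investigated during this trial as a marker for asthma control". The Discussion part of the abstract repeats this as a claim to novelty: "This is also the first study to investigate the use of FEV_1_/FEV_6_ as a marker for asthma control during pregnancy". The Background gives the motive, which is to tell pregnancy-related breathlessness apart from worsening asthma. The main Discussion returns to that difficulty and adds that "a target range for FEV_1_/FEV_6_ measurements during pregnancy could be identified".

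**The analysis.** The Data analysis section states: "FEV_1_/FEV_6_ trends will be described as these are observational data only". The next sentence reads: "Sensitivity and predictive validity of the ACQ would also be investigated".

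**The data.** Under Intervention (MCG participants), the ACQ is administered every month, and "The MCG will also have their FEV_1_/FEV_6_ measured monthly during the trial". Table 1 lists FEV1/FEV6 at baseline for both arms. The three- and six-month comparisons (Follow up, Table 3) do not include it.

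**The concern.** To support a measurement as a marker of asthma control, one has to show that it moves with control. The planned analysis looks only at how FEV1/FEV6 moves with time. Time in this trial is also gestation, and the Discussion itself expects the growing uterus to affect lung volumes. A falling or flat trend would therefore fit worsening control, advancing pregnancy, or both.

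The reason given for stopping at description is that the data are observational. That limits causal claims. It does not prevent estimating an association, which is what a marker question needs.

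The trial could thus finish with the monthly measurements in hand and no evidence on a question that its abstract presents as a first. A target range drawn from trends alone would have no link to control. The comparison of the two arms on the ACQ is not at stake.

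**Working it through.** **1. Aim against analysis**

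| Place | What it commits to |
|---|---|
| Abstract, Methods/design and Discussion | FEV1/FEV6 investigated as a marker of control |
| Background; Discussion | Separate pregnancy breathlessness from asthma; possible target range |
| Objective; Outcomes; Table 3 | FEV1/FEV6 not mentioned |
| Data analysis | Trends described; validity of the ACQ |
| Conclusion | FEV1/FEV6 explored as a lung-function measure |

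No row plans to relate FEV1/FEV6 to a measure of control. The section does not leave the method open: it names one and gives a reason for going no further. This is therefore not detail deferred to a fuller document.

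**2. The plan's own figure**

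The only sample-size figure concerns the ACQ: difference 0.5, SD 0.66, 80% power, two-sided 5%. The normal approximation gives 2 × (1.96 + 0.84)² × 0.66² / 0.5² = 27.3, rounded up to 28. The two-sample t-test gives 28.3, rounded up to 29, with 80.9% power at 29 per arm. The stated 29 reproduces. It says nothing about FEV1/FEV6.

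**3. What an added analysis could show**

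Inputs from the documents: 35 women recruited per arm and 20% attrition, leaving 35 × 0.8 = 28; monthly ACQ and monthly FEV1/FEV6 in the intervention arm.

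Assumed, not in the documents:
- Number of readings per woman, k. Baseline plus six monthly readings gives k = 7, which is a ceiling. Women may enrol through the second trimester, so some may deliver before six monthly visits. I therefore also take k = 4 and 5.
- The ACQ and FEV1/FEV6 of a given month can be paired. Both are monthly, but the text does not say they share a session.
- No serial correlation between a woman's monthly residuals.

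Formulas, for n women: within-woman df = nk − n − 1; SE of the within-woman correlation ≈ 1/√df; correlation detectable with 80% power at two-sided 5% ≈ tanh(2.8/√df).

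| n | k | df | SE | Detectable r |
|---|---|---|---|---|
| 35 | 7 | 245 − 35 − 1 = 209 | 0.069 | 0.19 |
| 28 | 7 | 196 − 28 − 1 = 167 | 0.077 | 0.21 |
| 28 | 5 | 140 − 28 − 1 = 111 | 0.095 | 0.26 |
| 28 | 4 | 112 − 28 − 1 = 83 | 0.110 | 0.30 |

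Adjusting for gestational age costs one more degree of freedom, which is immaterial. Serial correlation would worsen every row.

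For comparison, with one pair per woman and 28 women, an assumed correlation of 0.3 has a 95% interval of tanh(atanh 0.3 ± 1.96/√25), about −0.08 to 0.61. The repeated readings are what make the within-woman question worth asking.

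**The case against.** The best defence is that the article promises less than the abstract suggests. The trial is a pilot. The Objective does not mention FEV1/FEV6, and it is neither a primary nor a secondary outcome. The Discussion speaks of patterns and trends and of prompting further research, and the Conclusion treats the ratio as a measure of lung function, not a marker of control. Read that way, describing trends is a coherent hypothesis-generating aim, and only two abstract sentences are out of line. This stands as an argument for low severity, and for softening the abstract as an acceptable remedy. It does not remove the mismatch, because those two sentences state the aim plainly.

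Three stronger readings are tempting but unsupported.

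- *The ACQ validity analysis took the place of one meant for FEV1/FEV6.* The text says it is done as well, not in its stead. A slip in wording is possible but cannot be shown.
- *The ACQ sentence is wrong because it names no reference standard.* A condensed article commonly leaves that to the full protocol, and candidate criteria are collected (oral corticosteroid use, hospital visits). Nothing justifies deleting the sentence.
- *An ACQ score above 2 could serve as an event in the added analysis because the protocol already uses it.* It is used only as a notification trigger in the control arm at three and six months, whereas the monthly FEV1/FEV6 data are in the intervention arm.

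A fair objection to any added analysis also stands. In the intervention arm, an ACQ rise together with a documented exacerbation leads to a therapy review, and the Discussion envisages women adjusting management from home readings. Treatment may therefore respond to the very measures being related. This must be stated as a limit.

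**Conclusion.** The point holds as a minor one. The abstract states a marker aim, and the analysis fixed in the Data analysis section cannot address it, because trends alone do not separate asthma control from gestation. This rests on the text alone.

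The size of what is missing rests on assumptions. An exploratory within-woman analysis could detect a correlation of about 0.2 in the best case of seven readings per woman, and about 0.26 to 0.30 with five or four readings in 28 women, all before serial correlation. That is modest but adequate for an exploratory aim.

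A reader might infer that the trial formally tests FEV1/FEV6, or that its main result is compromised. Neither follows: the document says investigated and explored, and the ACQ comparison between arms does not depend on FEV1/FEV6.

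**What to change.** Keep the trend description and the ACQ validity sentence. Add to Data analysis an exploratory analysis in the intervention arm:

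- A linear mixed model of monthly FEV1/FEV6 on the ACQ score of the same month, adjusted for gestational age, with a random intercept per woman.
- Within-woman and between-woman ACQ effects separated (each woman's mean, and her deviation from it), reported as estimates with confidence intervals.
- If there are enough events, the accuracy of FEV1/FEV6 for an ACQ rise of 0.5 or more, with intervals that allow for repeated readings per woman.

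State the limits alongside: intervention arm only, therapy may change in response to the ACQ and to home readings, and modest precision.

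Alternatively, reword the two abstract sentences so that the aim is to describe FEV1/FEV6 values in pregnancy.

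The first option costs a few sentences and some analysis time, with no new data or procedures. The second costs only rewording.
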